### Objectives and hypotheses

The primary objective of this study is to investigate whether a twelve-week cognitively challenging PA intervention in children and adolescents with cancer has a positive effect on their EFs.

Secondary objectives are to investigate whether the twelve-week cognitively challenging PA program has a positive effect on cardiovascular health, motor abilities, body composition, psychosocial functioning, HrQoL and fatigue. Additionally, feasibility, safety, and adverse events of our PA program will be assessed. A PA counseling in maintenance therapy or aftercare will be offered to all participants, and its feasibility will be explored using qualitative interviews.

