### Study procedure and measurement time points

Participants will be enrolled in the study within the first three weeks after their cancer diagnosis. Subsequently to study inclusion, the baseline measurement will be conducted (T0). Afterwards, children in the IG will participate in a twelve-week cognitively challenging PA program. After six weeks, an interim measurement (T1) is carried out for both groups and again after twelve weeks at the end of the intervention (T2). To record possible long-term effects of the intervention, a follow-up measurement is carried out after six months (T3). At each of these four predefined and above-described measurement time points, all assessments will be conducted during a routine outpatient visit and/or during hospitalization (Fig. 1).

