#### Statistical analysis plan

Study sample characteristics will be shown separately as mean values (x̄) with its standard deviation (±) for each group regarding continuous variables. For categorical variables percentages and absolute numbers will be used. Normal distribution will be analyzed by the Shapiro-Wilk test and graphical verification of the Gaussian distribution. For all analyses, the significance level will be set at *p* < 0.05 and effect sizes will be provided.

*Preliminary analyses* will be performed to ensure that characteristics of the study participants (e.g., age, sex, diagnosis, weight, height) are comparable between the IG and CG using independent *t-*tests (continuous variables) or chi-squared tests (categorical variables). For feasibility analysis, descriptive statistics will be used.

The *main analyses* for the primary and secondary outcomes are repeated measures ANOVAs (for normal distributed data) and the Friedman test (for non-normally distributed data), where the “between-group” factor describes the IG vs. CG and the “within-group” factor is “timepoint” (T0, T1, T2, T3). If linear mixed models converge (despite small sample size), they will be used instead of repeated measures ANOVAs. These models will be specified to adjust for potential baseline imbalances [109]. They include the main effect of time and the group-time interaction. As the period between the data collection waves most probably will not be equal for all participants, as a time variable, the individual time interval in days will be used to increase the precision with which a child’s growth trajectory is measured. For each dependent variable, the optimal model will be determined using likelihood-ratio tests for nested models and Akaike information criterion for non-nested models. For these comparisons a random intercept model will be compared to a fixed effects model and a model including random intercepts and fixed effects. The model with the best fit will subsequently be chosen.

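### On its plainest reading, the preferred mixed model fits one straight line per group from T0 to T3, so T2 carries almost no weight and the 12-week effect is understated unless the groups keep diverging linearly to T3

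*Protocol article*

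**What the plan says.** Under Statistical analysis plan, the protocol article gives the mixed model priority over the ANOVA: "If linear mixed models converge (despite small sample size), they will be used instead of repeated measures ANOVAs". On the fixed effects it says: "They include the main effect of time and the group-time interaction". On the time scale it says: "as a time variable, the individual time interval in days will be used". The stated reason is that visit spacing will differ between children and that a growth trajectory is to be measured precisely. Model choice is by likelihood-ratio tests and AIC, but the comparison set concerns only the effects structure: "a random intercept model will be compared to a fixed effects model and a model including random intercepts and fixed effects". Baseline handling is left general: "These models will be specified to adjust for potential baseline imbalances".

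The ANOVA branch treats time differently. There, "the “within-group” factor is “timepoint” (T0, T1, T2, T3" are four levels of a factor. The sample size calculation also uses a within-between interaction with four measurements and two groups.

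The primary objective (Objectives and hypotheses) is to find out "whether a twelve-week cognitively challenging PA intervention in children and adolescents with cancer has a positive effect on their EFs". Under Study procedure and measurement time points, T1 is at six weeks, T2 is at twelve weeks when the intervention ends, and T3 has a separate role: "To record possible long-term effects of the intervention, a follow-up measurement is carried out after six months (T3". Whether those six months run from T0 or from T2 is not stated.

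**The concern.** If time is continuous and enters only as a main effect and an interaction with group, the group difference is forced to grow at a constant rate from T0 to T3. Supervised training stops at T2, so a plateau or fade afterwards is at least as plausible as continued divergence. T3 lies far from the other visits and therefore dominates the slope, while T2 sits close to the mean visit time and hardly affects it.

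Two things are at stake. The 12-week effect read from the model could be much smaller than the difference actually present at T2, and if the effect fades, a real benefit could be missed. In addition, the preferred model tests a 1-df slope difference, whereas the ANOVA branch and the sample size refer to a 3-df interaction. Whether the mixed model converges would then decide which hypothesis is tested.

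**Working it through.** **Inputs from the protocol.** T0, T1 and T2 at weeks 0, 6 and 12. T3 at six months, taken as week 26 (counted from T0) or about week 38 (counted from T2). Retest correlation rho = 0.8, alpha = 0.05, f = 0.105, N = 52 (26 per group), raised to 70 (35 per group) for losses.

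**Assumptions of this check.** Nominal visit times, complete data, compound symmetry, SD = 1. In the power example the true group difference is 0.25 SD at T1 and 0.5 SD at T2, with varying persistence at T3. The protocol gives none of these effect values.

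**1. The plan's own figure.** Noncentrality = N × 4 × f² / (1 - rho) = 52 × 4 × 0.011025 / 0.2 = 11.47, with 3 and (52 - 2) × 3 = 150 df. Power is 0.8105; N = 50 gives 0.793. The stated N = 52 is reproduced, for the 3-df interaction.

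**2. Weight of each visit in the slope.** With a random intercept and balanced data, the slope difference weights visit j by (t_j - mean t) / SS. Multiplying by 12 gives the weight in the implied 12-week effect.

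| | T0 | T1 | T2 | T3 |
|---|---|---|---|---|
| T3 at week 26: deviation from mean 11, SS = 372 | -11 | -5 | +1 | +15 |
| weight in 12-week effect | -0.355 | -0.161 | +0.032 | +0.484 |
| T3 at week 38: deviation from mean 14, SS = 840 | -14 | -8 | -2 | +24 |
| weight in 12-week effect | -0.200 | -0.114 | -0.029 | +0.343 |

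T2 carries 3% (week 26) or 4% (week 38, with a negative sign) of the total absolute weight. T3 carries 47% or 50%.

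**3. Implied 12-week effect as a share of the true T2 effect.** Half of the T2 effect is present at T1.
- Held at T3: 0.5 × (-0.161) + 0.032 + 0.484 = 0.44 (week 26); 0.5 × (-0.114) - 0.029 + 0.343 = 0.26 (week 38).
- Half left at T3: 0.5 × (-0.161) + 0.032 + 0.5 × 0.484 = 0.19; at week 38, 0.09.
- Gone by T3: -0.05 or -0.09, so the sign reverses.
- Straight-line divergence through T3: 1.00.

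**4. Power at 26 per group, 0.5 SD at T2, normal approximation.**
- SE of the T2-minus-T0 contrast = √(2 × 0.2 × 2/26) = 0.175; z = 0.5/0.175 = 2.85; power 81%.
- SE of the implied 12-week effect = 12 × √(0.2 × (2/26) / SS) = 0.077 (week 26) or 0.051 (week 38).
- Half left at T3: estimates 0.097 and 0.043 SD; z = 1.25 and 0.83; power 24% and 13%.
- Held at T3: estimates 0.218 and 0.129 SD; z = 2.82 and 2.50; power 81% and 71%.

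With 35 per group and no losses, the half-fade figures are 31% and 16% against 91%.

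**5. Sensitivity to baseline handling.** The listed fixed effects include no group main effect. With a common baseline at rho = 0.8, the T2 weights are +0.05 and -0.02. The shares are 45% and 27% if held, and 22% and 10% if half is left. Half-fade power at 26 per group is 31% and 18%. With baseline as a covariate and only T1 to T3 as outcomes, T2 still has the smallest share of the absolute weight, about 4% to 17%.

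**The case against.** The strongest reply is that the protocol never says the time effect is linear. A linear mixed model need not be linear in time, an optimal model is to be chosen by fit, and a condensed article may leave the shape of time to a full analysis plan. This stands in part: the straight line is inferred. However, the article does list the model terms and the comparison set, and neither contains an alternative time shape.

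A reader might infer that using actual days is itself the mistake. The documents do not support that. Uneven visit spacing is a sound reason for using days, and a piecewise term with a knot at T2 needs a continuous scale. The difficulty lies in the shape of time and the missing contrast.

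A reader might also take T2 as the declared primary timepoint. It is not. In the objective, twelve weeks describes the intervention, and the sample size covers all four visits. T2 is the natural reading because the intervention ends there.

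Low leverage of a visit near the mean time is also no defect in itself; it matters only if the true course is not a straight line. The Discussion hopes for sustained effects. If the group difference really grew linearly to T3, the slope would be unbiased and more powerful: scaled to f = 0.105 at N = 52, 92% against 32% (T3 at week 26) or 17% (week 38) for T2-minus-T0. A held gain is a different course, however, and under it the estimate is still too small.

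Finally, the ANOVA branch keeps visit as a factor, so the point concerns only the mixed model. That model takes precedence whenever it converges.

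**Conclusion.** The point holds in limited form. Followed on its plainest reading, the preferred model misstates the 12-week effect unless the groups diverge linearly through T3. It would report about 44% or 26% of the true T2 effect if the gain is held, and about 19% or 9% if half is left (T3 at week 26 or 38).

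It would go too far to say that the plan is bound to miss a real effect. The severe power loss belongs to fading effects, and the 0.5 SD half-fade course is an assumption of this check. With a held gain, slope power at 26 per group is about 81% or 71%, close to or moderately below the 81% of the direct contrast, and the damage is mainly to the estimate.

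The mismatch between the 1-df slope and the 3-df interaction needs no assumed effect course, only the straight-line reading. On that reading, the 80% power stated for the ANOVA does not carry over to the preferred model. The conclusion rests on three inferences: a straight line in days, T2 as the target, and nominal visit times.

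**What to change.** State the shape of time and the primary contrast before the data are analysed. Either use visit (T0, T1, T2, T3) as a factor with a group-by-visit interaction, or keep actual days with a piecewise term that has a knot at T2. Name the IG-CG difference in change from T0 to T2 as the primary contrast, with T1 and T3 secondary. With visit as a factor, handle uneven timing with a covariate for days off schedule or in a sensitivity analysis using actual days. State whether T3 is counted from T0 or from T2.

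The cost is analysis wording and a few more fixed-effect degrees of freedom than a single slope. If the true divergence is linear through T3, the T2 contrast also gives up power relative to the slope.

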### Statistical analysis

#### Sample size calculation

Two sample size calculations were performed for the primary outcomes: one encompassing both inhibition and cognitive flexibility and another for working memory. The calculation for the former is presented below, as it yielded the larger sample size needed, which was therefore selected for the study.

The sample size calculation was done using G*Power 3: Repeated measures ANOVA with four measurement points and two groups (within-between interaction), a statistical power of 80%, a small effect size (Cohen’s *f* = 0.105) [54], an α = 0.05 and a retest correlation of 0.8. This results in a minimum sample size of *N* = 52 in total, i.e. 26 subjects per group. To compensate for losses and drop-outs, we set the minimal sample size to *N* = 70.

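### The final mixed model for each outcome is chosen by fit from candidates that may omit the group-time term and that all lack a random slope or a correlation declining with time

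*Protocol article*

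**What the plan says.** All of this stands in the Statistical analysis plan section of the protocol article and covers primary and secondary outcomes.

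- When the mixed model applies: "If linear mixed models converge (despite small sample size), they will be used instead of repeated measures ANOVAs".
- Its terms: "They include the main effect of time and the group-time interaction".
- Its time variable: "the individual time interval in days will be used to increase the precision with which a child’s growth trajectory is measured".
- The criteria and their scope: "For each dependent variable, the optimal model will be determined using likelihood-ratio tests for nested models and Akaike information criterion for non-nested models".
- The candidates: "a random intercept model will be compared to a fixed effects model and a model including random intercepts and fixed effects".
- The decision: "The model with the best fit will subsequently be chosen".
- The error level: "For all analyses, the significance level will be set at *p* < 0.05 and effect sizes will be provided".

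The Study procedure section places the visits at baseline, six weeks, twelve weeks and a six-month follow-up. The Sample size calculation section assumes "Repeated measures ANOVA with four measurement points and two groups (within-between interaction), a statistical power of 80" per cent, with f = 0.105 and a single retest correlation of 0.8.

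**The concern.** There are two separate problems.

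**The candidate list against the stated terms.** The third candidate is distinguished from the first by having fixed effects as well as random intercepts. Taken literally, the first therefore has none, and so no group-time term. That term carries the treatment comparison. One sentence says the models contain it, the next offers a candidate that seems not to, and nothing says it is kept whatever the fit. The choice is made on the trial data and separately for each outcome, so the three executive-function tasks could also end with different models.

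**The covariance.** This does not depend on how the first candidate is read. The richest candidate has one random intercept, which forces the same correlation between visits six weeks apart and visits about six months apart. It also lets children differ in level but not in rate of change, although the plan speaks of each child's growth trajectory. If correlation falls with time or slopes vary, the standard error of the days-based group-time coefficient is too small and the test rejects too often.

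**Working it through.** **1. The plan's own figure.** For the within-between interaction, λ = f²·N·m/(1 − ρ), with df 3 and 3(N − 2).

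- N = 52: λ = 0.105² × 52 × 4 / 0.2 = 11.47, power 0.811.
- N = 50: power 0.793.
- N = 70: power 0.920.

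N = 52 reproduces and is not in dispute. The calculation uses one correlation for all visit pairs, so it says nothing about decline over time.

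**2. Type I error of the random-intercept model.** Inputs from the protocol: four visits at weeks 0, 6, 12 and T3, and a two-group comparison at 0.05 (two-sided assumed). Assumptions: T3 at week 26 or 38, because the origin of the six months is not stated; complete data; large-sample normal approximation.

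Let c be the visit times minus their mean and Σ the true covariance. With a group main effect in the model:

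- Variance the model reports is proportional to s_w = tr(PΣ)/3, where P removes the child mean.
- True variance is proportional, on the same scale, to v = c′Σc / c′c.
- R = s_w / v, and actual error = 2Φ(−1.96·√R).

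Worked case: T3 at week 26, correlation 0.8 at six weeks falling linearly to 0.6 at 26 weeks. The six correlations are 0.80, 0.74, 0.60, 0.80, 0.66 and 0.72, with mean 0.72.

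- s_w = 1 − 0.72 = 0.28.
- c = (−11, −5, 1, 15), c′c = 372, c′Σc = 160.32, so v = 160.32/372 = 0.431.
- R = 0.28/0.431 = 0.650, and 1.96 × √0.650 = 1.58, so the error is 11.4%.

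The plan names no group main effect, so the last column repeats the comparison of model-based with true variance without one. T3 is at week 26:

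| Assumed truth | With group main effect | Without |
|---|---|---|
| Equal correlation 0.8 | 5.0% | 5.0% |
| Random-slope SD 0.2 | 5.8% | 5.9% |
| Random-slope SD 0.3 | 6.8% | 7.1% |
| Random-slope SD 0.4 | 8.0% | 8.5% |
| Random-slope SD 0.5 | 9.4% | 10.2% |
| 0.8 falling to 0.7 | 8.7% | 8.1% |
| 0.8 falling to 0.6 | 11.4% | 10.2% |
| 0.8 falling to 0.5 | 13.4% | 11.5% |

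The random-slope rows take intercept variance 0.8, residual variance 0.2 and slope SD over the whole follow-up. Moving T3 to week 38 changes each entry by about 0.2 percentage points or less. Simulation at N = 70 agrees for the model without a group main effect: 5.4–5.7% under equal correlation and 5.7–9.7% for slope SD 0.2–0.5. Harsher first-order autoregressive patterns gave 11–17%; the conclusion does not rest on them.

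**3. How often a treatment-free candidate would win, if there is one.** Simulated at N = 70, T3 at day 182, equal correlation 0.8, and a slope difference of 0.2 SD over follow-up. The two candidates are nested, so the plan's likelihood-ratio test applies.

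- No common trend: the treatment-free model wins in 60% of trials.
- Common trend 0.1 SD: 19%.
- Common trend 0.3 SD or more: about 4% at most.

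As a check, the 2-df noncentral chi-square gives 58% (noncentrality 4.00) and 19% (9.78) for the first two. These rates are not all lost power. Without any selection, the standard error of the slope difference is about 0.139, so z = 0.2/0.139 = 1.44 and the test is significant in only about 30% of such trials.

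**4. Whether a pre-specified model repairs the error rate.** Simulated under equal correlation, autoregressive correlation and random slopes, a per-child slope t-test gave 4.0–5.6% and an unstructured-covariance test 4.3–6.0% (Monte Carlo SE about 0.5 points).

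**The case against.** **The treatment term is already protected.** The sentence naming time and group-time comes first, and the comparison can be read as concerning only the random-effects structure of models that hold those terms. That is a fair reading. A reader might infer that the plan allows the primary test to be deleted on grounds of fit; the text does not establish this, because it rests on one literal reading against an explicit sentence. What stands is that the two sentences conflict and need reconciling.

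**The selection figures need unfavourable conditions.** They do: a weak common trend. The plan itself expects growth, and a trend of 0.3 SD makes the risk negligible. The fixed-effects-only candidate was never chosen by AIC in simulation, so its neglect of repeated measures has no practical weight.

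**The inflation comes from an invented covariance.** The only correlation in the document is 0.8, and under equal correlation the error is about 5%. A reader might infer that the test runs at about twice its nominal rate. The documents do not support that as a fact; it holds only towards the upper end of the assumed range, and slope SDs of 0.2–0.3 give about 6–7%. The protocol does, however, lay out unequal visit gaps and a population mixed in diagnosis, age and treatment, so exactly equal correlation is not a safe default.

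**Covariance detail belongs in an analysis plan not shown.** Ordinarily yes. Here the article names the candidates, the criteria and the decision rule, so an analysis plan that follows it inherits the gap. Unstructured covariance is one sound option among several.

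**Conclusion.** The point holds at moderate severity. The plan fixes a fit-based choice of the final model for every outcome, primary ones included. Its candidate list conflicts with its own statement of the model terms, and nothing guarantees that the group-time term is kept. None of the candidates has a random slope or a declining correlation.

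The size depends on a covariance that the documents do not give. The days-based group-time test in the random-intercept model has about 5% type I error if correlation is 0.8 at all gaps, about 6–10% for random-slope SD 0.2–0.5, and about 8–13% if correlation falls from 0.8 at six weeks to 0.7–0.5 at T3. Loss of the treatment term is a material risk only on the literal reading and with a common trend below roughly 0.3 SD.

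**What to change.** Drop the fit-based choice of the final model and reconcile the two sentences. For the primary outcomes, state in advance:

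- one model that always keeps time and group-time, saying whether time enters the mean as days or as visits;
- a covariance that need not be exchangeable, for example unstructured over the four visits, or random intercept plus random slope;
- a small-sample degrees-of-freedom correction;
- a fallback if the model does not converge, such as a random intercept with robust standard errors.

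AIC or likelihood-ratio comparisons can remain for the covariance part alone, or as a reported sensitivity check. The change is to wording only and needs no further patients, visits or data. Its price is a few more covariance parameters and slightly wider intervals.

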For *supplementary analyses*, we will perform the same analyses for different age groups (6–11.99 and 12–17.99 years), cancer types (e.g. leukemia, brain tumors) and chemotherapy severity levels with sufficient sample size (*n* > 20). In addition, baseline performance will be correlated with gain scores using Pearson correlations (for normally distributed data) or Spearman correlations (for non-normally distributed data) for outcomes that show significant group × time interactions. To explore associated changes in certain variables, changes in motor abilities will be correlated with changes in core EFs and psychosocial functioning.

Additionally, for the intention-to-treat (ITT) analyses, we will perform two per protocol analyses. In the first per protocol analyses, only participants will be included, who did at least 80% of the PA sessions, in the second per protocol analyses participants will be included, if they completed 60% of training sessions. For all statistical analyses, the statistical program R and SPSS will be used.

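### Subgroups get separate significance tests and no stated test of difference, so at the planned effect an identical benefit would be significant in exactly one of two subgroups in about half of trials

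*Protocol article*

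**What the plan says.** The Statistical analysis plan section of the protocol article describes the main analysis as a group × time comparison over T0 to T3. It uses repeated measures ANOVA or the Friedman test, replaced by linear mixed models if these converge. The mixed models contain time and the group-time interaction, and no subgroup term is named.

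For the supplementary analyses, "we will perform the same analyses for different age groups" (two bands, split at 12 years). The same is planned for cancer types and for "chemotherapy severity levels with sufficient sample size", with sufficient defined as n > 20. One rule covers significance: "For all analyses, the significance level will be set at" p < 0.05, with effect sizes provided as well.

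The sample size section gives the inputs needed to judge these tests: "Repeated measures ANOVA with four measurement points and two groups (within-between interaction"), "a statistical power of 80"%, "a small effect size (Cohen’s *f* = 0.105") and "an α = 0.05 and a retest correlation of 0.8". The result is 52 children, 26 per group, raised to 70 for losses.

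**The concern.** Repeating a significance test inside each subgroup asks, separately for each, whether there is an effect there. It does not ask whether the effects differ. When each subgroup has moderate power, significance in one and not in the other is a common outcome even if the programme helps both equally. A reader shown one p-value on each side of 0.05 will tend to see an age-specific or diagnosis-specific benefit.

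The size threshold adds to this. The article treats more than 20 children as sufficient for a test that its own calculation sizes at 52.

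At stake is the reading of the subgroup results. Chance differences between age bands, cancer types or treatment intensities could be taken as findings.

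**Working it through.** **Inputs.** From the sample size section: f = 0.105, correlation ρ = 0.8, m = 4 visits, k = 2 groups, α = 0.05, N = 52 evaluable and 70 enrolled. From the analysis section: subgroup threshold n > 20, read as the subgroup total. The article does not give subgroup sizes. I assume two subgroups that together make up 52 to 70 children, each with at least 21, and arms balanced within each.

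**Formula.** For the within-between interaction, λ = f²·N·m/(1 − ρ), with df₁ = (k − 1)(m − 1) = 3, df₂ = (N − 2)·3 and sphericity assumed. Power is the probability that a noncentral F exceeds the 5% critical value.

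**Reproducing the plan's figure.** At N = 52, λ = 0.011025 × 52 × 4/0.2 = 11.47, df = 3 and 150, power 0.81. At N = 50, power is 0.793. The smallest even N reaching 80% is 52, as stated. At N = 70, power is 0.92.

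**Power within one subgroup at the same f.**

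| n | λ | df₂ | Power |
|---|---|---|---|
| 21 | 4.63 | 57 | 0.386 |
| 26 | 5.73 | 72 | 0.475 |
| 35 | 7.72 | 99 | 0.618 |
| 49 | 10.80 | 141 | 0.784 |

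**Chance that exactly one of two subgroups is significant, same true effect in both.** P = p₁(1 − p₂) + p₂(1 − p₁).

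| Split | Total | p₁ | p₂ | P |
|---|---|---|---|---|
| 35/35 | 70 | 0.618 | 0.618 | 0.472 |
| 30/40 | 70 | 0.541 | 0.685 | 0.485 |
| 26/44 | 70 | 0.475 | 0.732 | 0.512 |
| 21/49 | 70 | 0.386 | 0.784 | 0.565 |
| 21/39 | 60 | 0.386 | 0.672 | 0.539 |
| 26/26 | 52 | 0.475 | 0.475 | 0.499 |
| 21/31 | 52 | 0.386 | 0.557 | 0.513 |

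For example, at 21/49: 0.386 × 0.216 + 0.784 × 0.614 = 0.083 + 0.482 = 0.565. The range is about 47–57%.

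**Dependence on the true effect, 35/35 split.** No effect: 2 × 0.05 × 0.95 = 9.5%. Then 28% at f = 0.05, 45% at 0.075, 47% at 0.105, 30% at 0.13, 15% at 0.15 and under 1% at 0.20. With f = 0.105 but a correlation of 0.5, it is 40%.

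**Comparison with an interaction test.** In a simulation (4,000 runs per split, equal true effect of f = 0.105), a group × time × subgroup test at 0.05 was positive in 4.6% (35/35), 5.3% (26/26) and 5.3% (21/49) of runs. In the same runs, separate tests were significant in exactly one subgroup in 47.5%, 50.2% and 57.8%.

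**Power of that interaction test.** If one half of 70 children has f = 0.105 and the other half no effect, the noncentrality is 7.72/2 = 3.86 with df 3 and 198. Power is about 34%.

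**The case against.** Several points on the other side stand.

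- **Status of the analyses.** They are labelled supplementary, the objectives name no subgroup hypothesis, and the primary test is untouched. A reader might infer that the trial will declare a subgroup-specific effect. The article never says how discordant results would be read, so that is a risk of the method and not a stated intention.
- **What is already planned.** Effect sizes are promised for all analyses, which supplies part of what is needed, though not intervals or a test of difference. An unseen analysis plan may add an interaction term. But the article does state a method and a threshold, and the point is about that stated choice.
- **The size of the problem is conditional.** A reader might take about half as a general rate. It needs a true effect near the planned one and two qualifying subgroups. It is also calculated for repeated measures ANOVA, while the article prefers mixed models with time in days if they converge.
- **Meaning of n > 20.** A subgroup total is the natural reading, but the text does not say so. If it meant per arm, each subgroup would need at least 42, and two could not both qualify at 70.
- **Arm imbalance.** Because arm follows centre and phase, a reader might infer that a small subgroup could lie almost wholly in one arm. The documents do not support this. The Methods section has the sites swap roles after 1.5 years, and nothing links age, diagnosis or chemotherapy level to site or phase. If membership is unrelated to arm, a split of 4/17 or worse among 21 of 70 children (35 per arm) has a probability of about 0.1%.
- **Limits of the remedy.** With about 34% power in the example above, an interaction test would usually miss a real difference too. It guards against false claims of difference, not against missed ones.

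**Conclusion.** The point holds in a bounded form. The article plans separate tests at p < 0.05 within subgroups and states no test of whether the effect differs. At the plan's own effect size, correlation and visit number, with two qualifying subgroups totalling 52 to 70 children, an identical effect would be significant in exactly one of them in about 47–57% of trials. An interaction test would be falsely positive in about 5%. The discordance rate falls for true effects well away from f = 0.105, and is 9.5% when there is no effect.

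This rests on n > 20 being a subgroup total, balanced arms within subgroups, sphericity, and the repeated measures ANOVA used for sizing. It should be corrected because the stated method cannot answer the question that subgroup results invite. It does not threaten the primary conclusion.

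**What to change.** In the supplementary analyses:

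1. For each subgroup factor (age, cancer type, chemotherapy level), fit one model on all children with a group × time × subgroup term and its lower-order terms. Report the interaction estimate with its confidence interval.
2. Show the effect in each subgroup with its interval, descriptively. Label these results exploratory and make no separate significance claims.
3. State that n > 20 refers to the subgroup total (if so intended) and is a threshold for reporting, not a size adequate for testing, since power at n = 21 is about 39%.
4. State that a non-significant interaction will not be read as equal effects.

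The cost is analysis-plan wording; no extra children or data are needed. The drawback is that the interaction test has low power at 70 children and its intervals will be wide, which is an honest picture of what this trial can say about subgroups.

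### The supplementary correlation of baseline with gain scores is biased towards larger gains in weaker children when baseline and follow-up spread are similar, so testing it against zero cannot show differential benefit

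*Protocol article*

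**What the plan says.** The supplementary analyses in the Statistical analysis plan section state that "baseline performance will be correlated with gain scores using Pearson correlations", with Spearman as the alternative for non-normal data. This is done "for outcomes that show significant group × time interactions". The same section sets one threshold throughout: "For all analyses, the significance level will be set at *p* < 0.05".

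The text does not say whether the correlation is taken in the intervention group, in each group or in both pooled. It names no comparison with the control group's correlation and no correction for regression to the mean. It also does not say what will be concluded from the result.

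The Sample size calculation section uses "an α = 0.05 and a retest correlation of 0.8". Table 2 gives test-retest values of 0.62 (accuracy) and 0.72 (reaction time) for Hearts and Flowers, an intraclass correlation coefficient (ICC) of 0.92 for the Fish Flanker, and ICCs of 0.93 (children) and 0.76 (adolescents) for the Corsi task.

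**The concern.** The same baseline measurement sits on both sides of the correlation. A child who scores low at baseline partly by chance will tend to score nearer the average later, and so shows a larger gain without any extra benefit. Zero is then the wrong null value. Changing from Pearson to Spearman does not help, because the coupling is arithmetic and does not depend on the shape of the distribution.

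Restricting the analysis to outcomes with a significant group-by-time interaction does not remove the bias. That interaction concerns mean change, not whether the effect varies with baseline.

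A correlation of this kind is naturally read as evidence on which children gain most. If it is mostly an artefact, it could mislead later decisions about whom the programme suits.

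**Working it through.** **Inputs from the protocol.** Retest correlation 0.8, f = 0.105, four measurements and two groups (Sample size calculation); 35 children per group planned, 26 per group required before allowance for losses; reliabilities in Table 2. The significance level is 0.05, taken as two-sided.

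**Assumptions.** Bivariate normal scores, the same effect for every child, and the Table 2 reliabilities standing in for the baseline to follow-up correlation. The protocol gives no SDs, so the SD ratio is varied below.

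**Step 1. The plan's own figure.** The protocol states: "This results in a minimum sample size of *N* = 52 in total, i.e. 26 subjects per group". The noncentrality is f² × N × m / (1 − ρ) = 0.011025 × 52 × 4 / 0.2 = 11.47, with 3 and 150 degrees of freedom and sphericity assumed. Power is 81.1% at N = 52 and 79.3% at N = 50, so 52 is the smallest even N that reaches 80%. The figure is reproduced.

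**Step 2. Expected correlation with no differential benefit.** Let s be follow-up SD divided by baseline SD. Then

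r = (ρs − 1) / √(1 + s² − 2ρs), which at s = 1 becomes −√((1 − ρ)/2).

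- ρ = 0.92: −√0.04 = −0.20
- ρ = 0.80: −√0.10 = −0.32
- ρ = 0.72: −√0.14 = −0.37
- ρ = 0.62: −√0.19 = −0.44

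**Step 3. Falsely significant negative correlations at equal SDs.** Simulation, 40,000 trials per cell; the nominal rate in this tail is 2.5%.

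| ρ | n = 26 | n = 35 | n = 52 | n = 70 |
|---|---|---|---|---|
| 0.92 | 16% | 21% | 30% | 39% |
| 0.80 | 36% | 47% | 64% | 77% |
| 0.72 | 48% | 62% | 79% | 90% |
| 0.62 | 63% | 76% | 91% | 97% |

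The columns 26 and 35 are one arm after losses and as enrolled; 52 and 70 are both arms pooled. Fisher's z agrees: at ρ = 0.8 and n = 35, 0.3275 × √32 − 1.96 = −0.11, which gives 46%.

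The pooled columns leave out a difference in mean gain between arms. Such a difference changes little: 0.3 SD adds 0.3²/4 = 0.0225 to a gain variance of 0.40, so r moves from −0.32 to −0.2/√0.4225 = −0.31.

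**Step 4. Dependence on the SD ratio, ρ = 0.8.**

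- s = 0.9: −0.28/√0.37 = −0.46
- s = 1.0: −0.32
- s = 1.1: −0.12/√0.45 = −0.18 (false negative-tail significance 14%, 18% and 32% at n = 26, 35 and 70)
- s = 1.25: 0 (nominal error)
- s = 1.4: 0.12/√0.72 = +0.14

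The bias vanishes only at s = 1/ρ, which is 1.25 for ρ = 0.8, 1.61 for ρ = 0.62 and 1.09 for ρ = 0.92.

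**Step 5. An alternative.** A baseline-by-group interaction in a model for the follow-up score, with baseline as covariate, was simulated under the same uniform effect. It rejected in 4.8-5.1% of trials for ρ from 0.62 to 0.80 with 26 or 35 per group.

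**The case against.** A reader might infer that the trial will report that weaker children benefit more, and that the negative sign is inevitable. The documents support neither.

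- **No such conclusion is stated.** The protocol does not say how the correlation will be interpreted or that it will guide who is offered the programme. If it were shown separately by arm, the control group would display the same artefact.
- **The sign is conditional.** It depends on the SD ratio as well as on ρ. In a mixed sample under acute treatment, spread could move either way, and for the most reliable tests a follow-up SD about 9% larger already removes the bias.
- **A false finding is not certain.** At the plan's 0.8, in one arm of 26-35 children, it is somewhat less likely than not (36-47%). For the Fish Flanker at 0.92 it is 16-21%.
- **The reach is limited.** The analysis is supplementary, runs only after a significant interaction, and touches no effect estimate.
- **The alternative has limits.** Power is modest: at ρ = 0.8 and equal SDs, about 21-26% for a slope difference of 0.2 SD per SD and 61-76% for 0.4, with 26-35 per arm. Allocation is by centre and phase, so arms may differ in diagnosis mix or reliability, and their slopes may differ for that reason.

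All of this stands and sets the size of the point. It does not rescue the test. Zero is the correct null only at one particular SD ratio for each ρ, and the protocol gives no reason to expect that ratio.

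**Conclusion.** The point holds as a bias in a supplementary analysis. With similar SDs at the two visits, the planned correlation leans towards larger gains in weaker children whether or not benefit depends on baseline, and a test against zero cannot separate the two. At equal SDs and across the Table 2 range of 0.62 to 0.92, the false-significance rate is between 16% and 97% depending on reliability and on whether 26 or as many as 70 children are analysed; at the plan's own 0.8 it is 36-77%. These rates fall if the follow-up SD exceeds the baseline SD and rise if it is smaller. For reaction time, where lower is better, the sign depends on how gain is coded, but the artefact still favours weaker performers. The planned main analyses and the sample size of 52, raised to 70, are not affected. The analysis should be changed before the data are examined.

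**What to change.** Replace the correlation with a baseline-by-group interaction in a model for the follow-up score at the visit from which gain would have been computed, with baseline as covariate. Label it exploratory and report the slope difference with its confidence interval. Regression to the mean acts in both arms, so with comparable arms the difference in slopes, not the slope in one arm, addresses whether benefit depends on baseline.

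State two limits beside the result: power is low with 26-35 children per arm, so a null result is not evidence of a uniform benefit; and because allocation is by centre and phase, a slope difference may also reflect case mix. Keeping the restriction to outcomes with a significant group-by-time interaction is optional, since the coupling is corrected either way.

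The cost is one model term and a few sentences of text. It needs no new data, visits or participants.
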